**C. TPT uptake**		
Number screen-negatives prescribed TPT	# screen-negatives prescribed TPT (baseline screen-negatives prescribed TPT ~ study staff-prescribed TPT)	None
Proportion screen-negatives prescribed TPT	# screen-negatives prescribed TPT	# randomized to corresponding study arm
Number screen-positives prescribed TPT	# screen-positives prescribed TPT (baseline screen-positives prescribed TPT ~ routine clinician-prescribed TPT)	None
Proportion screen-positives prescribed TPT	# screen-positives prescribed TPT	# randomized to corresponding study arm
Number initiated on TPT	# screen-negatives prescribed TPT + # screen-positives prescribed TPT	None
Proportion initiated on TPT	# screen-negatives prescribed TPT + # screen-positives prescribed TPT	# randomized to corresponding study arm
Time to TPT initiation	Days from baseline TB screening to initiation of TPT	
Number completing TPT (measured by pill count, self-reported adherence)	# initiated on TPT who completed ≥90% of treatment over prescribed TPT period	None
Proportion completing TPT (measured by pill count, self-reported adherence)	# initiated on TPT who completed ≥90% of treatment over prescribed TPT period	# randomized to corresponding study arm
**D. Prevalent TB diagnosis**		
Number microbiologically confirmed prevalent TB cases detected by the screening test	# screen-positives diagnosed with prevalent TB (diagnosed = a positive urine LAM result, one non-trace positive or two trace-positive Xpert Ultra results ≤3 months of study entry)	
Proportion microbiologically confirmed prevalent TB cases detected by the screening test	# screen-positives diagnosed with prevalent TB	# randomized to corresponding study arm
Number microbiologically confirmed prevalent TB cases missed by the screening test	# screen-negatives diagnosed with prevalent TB	None
Proportion microbiologically confirmed prevalent TB cases missed by the screening test	# screen-negatives diagnosed with prevalent TB	# randomized to corresponding study arm
Number diagnosed with microbiologically confirmed prevalent TB	# screen-positives diagnosed with prevalent TB + # screen-negatives diagnosed with prevalent TB	None
Microbiologically confirmed TB prevalence	# screen-positives diagnosed with prevalent TB + # screen-negatives diagnosed with prevalent TB	# randomized to corresponding study arm
**E. Prevalent TB treatment**		
Number treated for prevalent TB	# treated (treated = initiated on TB treatment ≤3 months of study entry regardless of Xpert Ultra result)	None
Proportion treated for prevalent TB	# treated	# randomized to corresponding study arm
Number with microbiologically confirmed prevalent TB completing treatment	# diagnosed AND treated who complete treatment (complete treatment = clinic TB treatment records confirm treatment completion)	None
Proportion with microbiologically confirmed prevalent TB completing treatment	# diagnosed AND treated who complete treatment	# diagnosed
Time to treatment of microbiologically confirmed prevalent TB	Days from prevalent TB diagnosis to initiation of TB treatment	

### Sample size

The sample size calculations are primarily based on the primary objective (which requires a larger sample size). We expect 2-year mortality of 5.2% and 2-year TB incidence of 7.3% in the control arm [4, 28]. Assuming a two-sided alpha of 0.05 and 12% lost to follow-up, a sample size of 860 participants per arm (1720 total) will provide 80% power to detect a relative reduction of 35% in the 2-year combined outcome (from 12.5% [*n* = 95] to 8.1% [*n* = 62]). This sample size will also provide 85% and 90% power if 2-year mortality is 6.8% and 8.8%, respectively (Table 3). This sample size also gives 80% power to detect a smaller 29% relative reduction if the 2-year combined TB incidence and mortality in the control arm is as high as 17.5% with a 10% loss to follow-up. We will analyze the primary outcome as time-to-event and therefore expect this study power assuming binary outcomes will be a lower bound for study power.

**Table 3 Tab3:** Power calculations (power to detect 35% difference in the combined 2-year TB incidence and mortality outcome when 2-year TB incidence is 7.3%)

2-year mortality		Power
POC CRP-based screening	Symptom-based screening	
3.4%	5.2%	0.80
4.4%	6.8%	0.85
5.1%	7.9%	0.88
5.7%	8.8%	0.90

For the secondary objective, based on published estimates of specificity from similar settings, we estimate no more than 15% of all patients in the control arm will initiate 3HP (and 13.5%, or 90% of all control patients initiating 3HP, will complete 3HP) [16, 17, 20]. This sample size will give more than 90% power to show improvements in the proportion of all patients initiating 3HP by an absolute difference of 6% of more, which is much less than what is considered clinically important; we anticipate 55% of all patients in the POC CRP will initiate 3HP (and 55% of all patients will complete 3HP).

### Random allocation

Randomization lists were generated in R using Chen’s design with a biased coin and maximum tolerated imbalance, stratified by site [29]. Within each site, sequentially numbered pre-printed forms with each participant arm allocation were inserted into opaque envelopes, which were sealed and sequentially numbered. Randomization is implemented by the trained study staff member opening the next unopened envelope in sequence revealing the randomization arm assigned to the participant, only after all eligibility criteria have been assessed and the participant has been found to be eligible.

### Blinding

TB SCRIPT is a single-blinded trial. We will not be blinded to intervention allocation, as we will perform baseline TB screening and subsequent procedures based on the results of screening (e.g., 3HP initiation for eligible screen-negative participants). Participants and routine clinic staff will be blinded, as will the study principal investigators (except for the trial statistician). To facilitate blinding, all participants will undergo a finger prick and have capillary blood measured for CRP (intervention) or beta-human chorionic gonadotropin (β-hCG; control, regardless of gender). POC CRP and β-hCG assays will be provided by BodiTech, Med Inc. and measured using the iCHROMA Reader which provides analysis of more than 30 unique markers, including CRP and β-hCG. There are no procedures for unblinding, as clinicians are free to order TB testing, initiate TB treatment, or initiate TPT for study participants at any time.

### Data collection

#### Medical record review

All participating clinics will use standardized electronic case report forms for initial and follow-up visits. At the baseline visit, we will administer a standardized questionnaire to verify relevant information in the medical record including demographic data, TB and other opportunistic infection history, current medications, and routine lab measurements. At follow-up visits, we will review the medical record to extract relevant interval medical history (e.g., TPT-related adverse events, incident TB diagnosis), new medications (e.g., clinician-initiated active TB treatment or TPT), and routine lab measurements (e.g., HIV viral load) using a standardized form.

#### TPT and TB treatment adherence monitoring

For participants receiving 3HP, we will assess adherence by performing pill counts and patient-reported adherence. In addition, we will review the medical record and record the number of 3HP refill visits completed. For participants receiving active TB treatment, we will review clinic TB treatment records and record the number of treatment months recorded as complete.

#### Prevalent TB status assessment

For all participants who screen-positive by their assigned TB screening strategy, we will collect urine and 2 spot sputum specimens for urine LAM (Alere Determine TB-LAM) and sputum Xpert Ultra testing. All urine LAM-negative participants and urine LAM-positive participants with risk factors for drug-resistant TB (history of prior TB treatment, contact with a known drug-resistant TB case) will have sputum tested by Xpert Ultra for rapid detection of rifampin resistance. All participants with a positive urine LAM and/or sputum Xpert Ultra result (including trace-positives) will be referred to routine clinic staff for initiation of anti-TB treatment. Additionally, for participants with trace-positive Xpert Ultra results, we will perform repeat Xpert Ultra testing on the second spot sputum specimen. Participants with a non-trace-positive Xpert Ultra result or two trace-positive Xpert Ultra results will be classified as having active prevalent TB.

#### Final TB status assessment

For all participants who have not taken anti-TB treatment during follow-up, we will collect 2 spot sputum specimens at the final (24 months) study visit for sputum Xpert Ultra testing; repeat Xpert Ultra testing, if the initial test is trace-positive; and liquid culture and drug susceptibility testing (DST). Speciation testing will be performed on all positive cultures to confirm the presence of *M. tuberculosis* complex using Ziehl-Neelsen smear microscopy for detection of acid-fast bacilli and SD MPT64 (Standard Diagnostics Bioline TB Ag MPT64, South Korea) for rapid *M. tuberculosis* antigen detection. DST will include susceptibility testing to all first-line TB medications including isoniazid and rifamycin-based drugs. Participants will be classified as having incident TB if at least one of the following criteria are met: at least one sputum culture positive for *M. tuberculosis* complex, one non-trace-positive Xpert Ultra result, or two trace-positive Xpert Ultra results.

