##### Screen-positive participants

We will collect spontaneously voided urine and spot sputum specimens (induced, if necessary) from all screen-positive participants (POC CRP ≥8 mg/L in the intervention arm; presence of ≥1 symptom in the control arm) for urine LAM (Alere Determine TB-LAM) and sputum Xpert Ultra testing. In accordance with current WHO guidelines, sputum Xpert Ultra testing will be performed if (1) urine LAM is negative or (2) urine LAM is positive and the participant has risk factors for drug-resistant TB (prior TB treatment, contact with drug-resistant TB case). Participants who test positive for TB by urine LAM and/or sputum Xpert Ultra will be referred to clinicians for TB treatment initiation. To maximize real-world relevance, sputum will not be submitted for mycobacterial culture because most HIV programs in high burden countries use Xpert (standard cartridge or Ultra) as the confirmatory test for TB. Participants who screen-positive but test negative by urine LAM and sputum Xpert Ultra will not be given 3HP at the time of enrollment (as their risk of active TB remains non-negligible), but will be eligible for TPT initiation at the discretion of treating (non-study) clinicians throughout the follow-up period.

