**A. TB incidence**		
Number diagnosed with microbiologically confirmed incident TB within 2 years	# diagnosed with incident TB (incident TB = positive non-trace Xpert Ultra result, two trace Xpert Ultra results, or ≥ 1 positive culture result > 3 months after study entry)	None
2-year incidence of microbiologically confirmed TB	# diagnosed with incident TB	# randomized to corresponding study arm - # treated for prevalent TB (prevalent TB = active TB diagnosed ≤3 months of study entry)
Time to microbiologically confirmed incident TB diagnosis	Days from 3 months post-enrollment to incident TB diagnosis (or censoring)	
Incident rate of microbiologically confirmed TB	# diagnosed with incident TB	(# randomized to corresponding study arm - # treated for prevalent TB)/time in person-years
Number diagnosed with drug-resistant incident TB within 2 years	# diagnosed with incident drug-resistant TB (drug-resistant TB = DST-detected resistance to drugs administered for TPT [e.g., isoniazid])	None
2-year incidence of drug-resistant TB among people receiving TPT	# diagnosed with incident drug-resistant TB	# received TPT of any duration

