### Statistical methods

#### Primary and secondary outcomes

The primary trial outcome is a 2-year composite endpoint of microbiologically confirmed incident TB and all-cause mortality, measured as time to first diagnosis of incident TB or death from any cause. The primary analysis will be by intention-to-treat (ITT), including all participants randomized without regard to the results of baseline TB screening, and we will use a two-sided alpha (0.05 significance) in assessing the effect of the intervention on the primary outcome. Participants with prevalent TB will be included in the analysis to preserve the randomized groups (the ITT principle) but excluded from the outcome of incident TB because subsequent disease is more likely to represent relapse or failure (and these participants will not routinely receive TPT). Time from randomization to first event (diagnosis of incident TB or death from any cause) will be analyzed using the log rank test and Cox proportional hazards models, adjusted for the study site. If data are missing or a patient is lost to follow-up, a patient’s data will be censored in the analysis at the date of last known contact. We will also use the Mantel-Haenszel method to determine standardized incidence rates and incidence rate differences. Balance at baseline on all known and suspected prognostic factors will be assessed, and if important imbalances are found (e.g., differences in median baseline CD4 count), a sensitivity analysis will be conducted using a Cox model to adjust for these factors. We will also assess the impact of clinician-initiated co-interventions (e.g., clinician-initiated TPT, clinician-initiated TB treatment) on the primary outcome. We will conduct a sensitivity analysis in which these participants are censored as soon as they are initiated on TPT or TB treatment by non-study clinicians. Standard checks for variation by enrollment site will also be planned. Secondary outcomes for the primary objective include the individual primary endpoints (TB incidence and mortality analyzed separately) and 2-year isoniazid-resistant TB incidence and will be analyzed using a similar approach; there will be no adjustment for multiplicity since these are pre-specified secondary outcomes.

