We will repeat the primary analysis in the following pre-specified sub-groups: by age, gender, enrollment site, and CD4 strata (< 50, 50–199, ≥200 cells/μL). Safety data related to missed diagnoses of prevalent TB, acquired drug-resistant TB, and TPT-related serious adverse events will be tabulated by study arm.

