### Data monitoring committee

An independent DMC that includes experts in TB diagnostics and the analytical and regulatory aspects of clinical trials met by conference call before enrollment and will meet at 25%, 50%, 75%, and 100% enrollment and when 50% of patients have completed follow-up and when 100% have completed follow up to review safety data from the trial. They are charged with evaluating the quality of trial administration, monitoring safety issues, and providing guidance on scientific, methodological, and ethical issues. Specifically, the DMC will review administrative reports prepared by the Data Manager for each meeting of the DMC. This report will describe study progress, including the following: (1) accrual, (2) demographics, (3) subject status, (4) TB prevalence, (5) proportion of patients initiating TPT, (6) number and type of serious AEs (SAE), (7) cumulative TB incidence (including drug-resistant TB), and (8) cumulative all-cause mortality. Tables by arm will be prepared for review in the closed sessions of the DMC meetings; the DMC will have access to screening assignments. Differences in the composite primary trial outcome (2-year TB incidence and 2-year mortality) between trial arms are unlikely to modify our study protocol because of the long duration of follow-up (2 years), relative to recruitment. However, differences in missed diagnoses of prevalent TB (primary risk and safety endpoint), measured as the proportion of microbiologically confirmed prevalent TB cases missed by screening, will be carefully reviewed and the decision to continue enrollment after each meeting will be made by the DMC. Although unlikely, the DMC should inform the PIs if, in their view, the results of an interim analysis are likely to convince a broad range of clinicians (including those supporting the trial and the general clinical community) that, on balance, one trial arm is clearly indicated or contraindicated for all participants or a particular category of participant. Further details of stopping guidelines and roles and responsibilities of members are included in the DMC charter.

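### Isoniazid susceptibility testing is planned only at month 24 in participants untreated for TB, so the 2-year drug-resistance outcomes are under-ascertained and resistance cannot be called acquired

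*Protocol article*

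**What the plan says.** All references are to the protocol article.

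- **When culture and DST are done.** Under Final TB status assessment, the sampling rule reads: "For all participants who have not taken anti-TB treatment during follow-up, we will collect 2 spot sputum specimens at the final" visit, which falls at month 24. The same section states that "DST will include susceptibility testing to all first-line TB medications including isoniazid and rifamycin-based drugs". Table 1 marks culture and DST once, in the month-24 column.
- **Baseline.** Under Screen-positive participants, "sputum will not be submitted for mycobacterial culture"; the stated reason is real-world relevance. Xpert Ultra is described there and under Prevalent TB status assessment, and the only resistance it is said to detect is to rifampin. Screen-negative participants, who are the ones offered 3HP, have no sputum taken at entry.
- **What counts as incident TB.** Under Outcomes, a positive culture, Xpert Ultra result (one non-trace or two trace) or urine LAM result from month 3 onwards. Table 2 omits LAM but still accepts Xpert Ultra without culture.
- **What counts as drug-resistant TB.** Table 2: "drug-resistant TB = DST-detected resistance to drugs administered for TPT [e.g., isoniazid". The incidence row divides such cases by everyone who received any TPT.
- **How it is analysed.** Statistical methods lists "2-year isoniazid-resistant TB incidence and will be analyzed using a similar approach" to the primary analysis, and among the safety data "acquired drug-resistant TB, and TPT-related serious adverse events will be tabulated by study arm".
- **What the DMC sees.** The report content includes "cumulative TB incidence (including drug-resistant TB").

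**The concern.** The outcome is named for a two-year period, but the only study test that can reveal isoniazid resistance is made at one moment, in a subgroup defined by not having been treated for TB. Someone diagnosed and treated at, say, month 8 is an incident case, yet gets no month-24 sputum and has no other isoniazid test described.

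This matters because of where the risk lies. Risks to study participants names acquired resistance in missed TB started on 3HP as a potential harm. 3HP is 12 weekly doses beginning no earlier than two weeks after ART, so it runs to about month 3 at the earliest. Missed TB that surfaces during or soon after 3HP would be diagnosed in routine care. Up to month 3 it is classed as prevalent; after that it is an interim incident case. No isoniazid test is described for either. A low or equal count of resistant cases could then be reported as a reassuring two-year incidence when many of the relevant cases were never tested.

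The word *acquired* makes a further claim: that the organism was susceptible at entry. Nothing planned at entry can show that.

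**Working it through.** **1. Anchor to the plan's own figures (Sample size).** Inputs: 860 per arm, 12% loss, control composite 12.5%, relative reduction 35%, two-sided alpha 0.05.

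- Evaluable per arm: 860 × 0.88 = 756.8.
- Events: 756.8 × 0.125 = 94.6 (stated 95); 756.8 × 0.125 × 0.65 = 61.5 (stated 62).
- Two-proportion power without continuity correction: 0.800 (stated 80%).

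The stated figures reproduce and are not in dispute.

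**2. Expected incident TB.** Control 2-year TB incidence is 7.3%. I apply the 35% reduction to TB alone (assumption).

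- Control: 756.8 × 0.073 = 55.2.
- CRP: 55.2 × 0.65 = 35.9.
- Total: about 91.

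**3. Which cases have a planned isoniazid result.**

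| Case | Confirmed by | Planned isoniazid DST |
|---|---|---|
| Diagnosed and treated between month 3 and month 24 | Xpert Ultra, LAM or routine culture | None described |
| Found at the month-24 visit, no earlier TB treatment | Xpert Ultra or culture | Yes, if culture grows |

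Table 1 banks only serum/plasma and urine, so no stored sputum is described for later testing.

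**4. Size.** Let m be the share of incident cases found at month 24. The document does not give m. Cases with no planned result = 91.2 × (1 − m).

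| m (assumed) | No planned result |
|---|---|
| 75% | 22.8, about 23 |
| 50% | 45.6, about 46 |
| 25% | 68.4, about 68 |

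**5. Effect on Table 2's incidence row.** The numerator needs a DST result; the denominator does not. An untested case in a TPT recipient is therefore counted below the line and can never be counted above it. With the planned 3HP uptake (15% control, 55% CRP), the denominators are about 860 × 0.15 = 129 and 860 × 0.55 = 473, before any clinician-initiated TPT. Each untested case leaves 1/129 = 0.78 percentage points of uncertainty in control and 1/473 = 0.21 in CRP.

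**6. Effect on the comparison.** If the true resistance risk is equal and a fraction f of cases is treated before month 24, the apparent risk ratio (CRP/control) is (1 − f in CRP) / (1 − f in control).

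- f = 40% CRP, 60% control: 0.60 / 0.40 = 1.5.
- Reversed: 0.40 / 0.60 = 0.67.

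Both values of f are assumptions, and the direction is unknown.

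**7. DMC timing (Trial status).** Enrolment began on 16 November 2020, so the first month-24 visits fall in November 2022. On 20 October 2021, 491 were enrolled. Reaching 75% (1,290) needs 799 of the remaining 1,229, or 65%. If recruitment is steady to December 2022, that point comes in about July or August 2022. The 25%, 50% and 75% enrolment reviews therefore precede any month-24 result, and the 100% review can have very few.

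**The case against.** A reader might infer that two-year isoniazid-resistant TB cannot be measured at all. The document does not support that. Month-24 cases are tested and counted, Outcomes accepts a culture diagnosis from month 3, and Medical record review extracts incident TB diagnoses, so a routine DST result could enter. None is planned or described, but the accurate term is under-ascertained.

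A reader might also infer that the plan classes untested cases as non-resistant. Statistical methods states no such rule; its only relevant provision is censoring at last contact. What stands is narrower: Table 2's own numerator and denominator have that effect for TPT recipients.

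Nor will the DMC be without resistance data throughout. The report item says drug-resistant, not isoniazid-resistant; Xpert Ultra gives rifampin results, and 3HP contains a rifamycin. The DMC also meets at 50% and 100% completed follow-up, when month-24 results will exist. Only the enrolment-stage isoniazid gap stands.

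Two further points carry weight. The article condenses a fuller protocol, which may say how interim cases are tested. And clinic staff are blinded, which limits differences between arms in when TB is diagnosed. Neither removes the mismatch between the procedures and the outcome labels that the article does state: it sets out a full schedule with baseline and final TB assessments, and it expressly rules out baseline culture. Blinding is also only partial protection. Participants on 3HP have extra visits that include TB screening, and far more of them are expected in the CRP arm.

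Finally, the 91 cases cover all incident TB in both arms, not only TPT recipients.

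**Conclusion.** The point holds as one of ascertainment and labelling. As described, the drug-resistant TB outcomes in Table 2 and the two-year isoniazid-resistant incidence in Statistical methods capture isoniazid resistance mainly in TB still untreated at month 24. That is closer to a month-24 prevalence than to a two-year incidence. Any difference between arms in the timing of diagnosis would bias the comparison, in a direction the document does not let us predict.

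About 23 to 68 of roughly 91 expected cases would lack a planned result. That range simply reflects the assumed 75% to 25% found at month 24, and the 91 assumes that the 35% reduction applies to TB alone. The description of resistance as acquired is unsupported whatever that share is, because no baseline isolate exists to compare.

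The consequence is confined to what the trial can conclude about resistance.

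**What to change.** - **Table 2 and Statistical methods:** label the outcome as isoniazid resistance detected among incident TB cases with a DST result.
- **Reporting:** give, by arm, the number of incident cases with and without a result. Treat untested cases as missing, not as non-resistant. On Table 2's denominators, add a best case (none of the untested resistant) and a worst case (all resistant).
- **Safety tabulation:** replace acquired drug-resistant TB with drug-resistant TB detected in incident cases.
- **Data monitoring committee section:** state that month-24 isoniazid DST results will not be available at the 25%, 50% and 75% enrolment reviews, and will inform the later follow-up reviews.

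The cost is wording, one extra table row per arm and a narrower resistance claim. Culturing interim cases before treatment would close more of the gap, but it needs new clinic procedures and is not part of this recommendation. While these passages are open, the sponsor should also reconcile Outcomes, which limits DST to participants who received TPT, with Final TB status assessment, which does not. That is a separate inconsistency.

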### Outcomes

The primary trial endpoint is a composite outcome of microbiologically confirmed incident TB and all-cause mortality, measured as time to first diagnosis of incident TB or death from any cause. Microbiologically confirmed incident TB is defined as active TB diagnosed by either culture, one non-trace positive Xpert Ultra result or two trace-positive Xpert Ultra results, or positive urine LAM result from 3 months after randomization to the end of follow-up (at 2 years, or at the time of last contact for participants who are lost to follow-up). To assess active TB status at the end of follow-up, 2 spot sputum specimens will be collected from all participants who have not taken anti-TB treatment during the study at the final (24 months) study visit for sputum Xpert Ultra testing, liquid culture, and drug susceptibility testing (for participants who received any TPT). Secondary outcomes are presented in Table 2.

**Table 2 Tab2:** Secondary outcomes of the TB SCRIPT trial

Outcome	Numerator	Denominator

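### The lists of results that confirm TB disagree on urine LAM and culture, and none says how a positive standard-cartridge Xpert is classified

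*Protocol article*

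**What the plan says.** The protocol article defines microbiologically confirmed TB in several places.

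- **Outcomes, primary endpoint (month 3 to end of follow-up):** "active TB diagnosed by either culture, one non-trace positive Xpert Ultra result or two trace-positive Xpert Ultra results, or positive urine LAM result".
- **Table 2, part A (incident TB):** "positive non-trace Xpert Ultra result, two trace Xpert Ultra results, or ≥ 1 positive culture result > 3 months after study entry".
- **Final TB status assessment (month 24):** at least one positive culture, "one non-trace-positive Xpert Ultra result, or two trace-positive Xpert Ultra results".
- **Table 2, part D (prevalent TB, first 3 months):** "diagnosed = a positive urine LAM result, one non-trace positive or two trace-positive Xpert Ultra results".

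On who tests, the Blinding section says that "clinicians are free to order TB testing, initiate TB treatment, or initiate TPT for study participants at any time". Participant timeline hands all care after baseline to routine clinic staff. Medical record review has the study "extract relevant interval medical history (e.g., TPT-related adverse events, incident TB diagnosis" and similar items at follow-up visits. On the assay, the section on screen-positive participants justifies omitting baseline culture by saying that "most HIV programs in high burden countries use Xpert (standard cartridge or Ultra) as the confirmatory test for TB".

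Outcomes and Final TB status assessment limit month-24 sputum sampling to participants who have not taken anti-TB treatment. The Data monitoring committee section makes missed prevalent TB the primary risk and safety endpoint and ties the decision to continue enrolment to it.

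**The concern.** Each definition is a closed list, so a result that is not named does not count. The lists differ from one another. None covers the standard Xpert cartridge, which the protocol itself names as a confirmatory test in routine programmes.

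Between baseline and month 24, detection of TB rests on tests ordered in routine care. The same is true of missed prevalent TB: the study does confirmatory testing at baseline only in screen-positive participants, so a screen-negative participant with TB in the first 3 months is found only if a clinic tests.

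At stake are the count of primary events, the agreement between the composite and its TB component, and the count of missed cases that the monitoring committee reviews.

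**Working it through.** **1. The lists side by side**

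| Place | Window | Culture | 1 non-trace or 2 trace Ultra | Urine LAM | Standard-cartridge Xpert |
|---|---|---|---|---|---|
| Outcomes (primary) | month 3 to 24 | yes | yes | yes | no |
| Table 2, part A | after month 3 | yes | yes | no | no |
| Final TB status assessment | month 24 | yes | yes | no | no |
| Table 2, part D | up to month 3 | no | yes | yes | no |

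The classifying sentence in Prevalent TB status assessment names Ultra results only. It therefore also differs from part D on LAM.

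**2. Four participants followed through the text**

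- *Positive only by urine LAM in care at month 9.* A primary event under Outcomes, but not incident TB under Table 2 part A. The TB component then does not reconcile with the composite.
- *Screen-negative, positive only by culture in care at week 8.* Not a missed prevalent case in Table 2 part D, and too early to be incident. Part A's own note on prevalent TB sets no test restriction, and part E counts treatment whatever the Ultra result, so the case can appear there. It is lost from the part D count.
- *Positive only by standard-cartridge Xpert in care at month 9, then treated.* Matches no list. Because of the treatment, there is no month-24 sputum. The participant stays event-free unless he or she dies. The sensitivity analysis on clinician-started TB treatment censors this person and does not count an event.
- *Positive by non-trace Ultra in care at month 9.* Counts under Outcomes and part A. Neither requires that the study ordered the test.

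**3. The protocol's power figure**

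Inputs from Sample size: 860 per arm, 12% lost, control mortality 5.2% plus TB 7.3% = 12.5%, relative reduction 35%, two-sided alpha 0.05.

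- n = 860 × 0.88 = 756.8 per arm; p1 = 0.125; p2 = 0.125 × 0.65 = 0.08125; mean p = 0.103125.
- z = [(p1 − p2)√n − 1.96√(2p(1 − p))] / √(p1(1 − p1) + p2(1 − p2)), with p the mean.
- z = (0.04375 × 27.51 − 1.96 × 0.4301) / 0.4290 = 0.84, so power is 0.80.
- Expected events are 94.6 and 61.5 (stated 95 and 62).

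The stated power is reproduced.

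**4. Illustrative loss**

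The protocol gives no share of TB confirmed only by an unlisted test. Assume a share f of TB events is lost, equally in both arms, with the 35% reduction unchanged. The control composite is then 0.052 + 0.073(1 − f).

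| f | Control composite | CRP arm | Control events lost (756.8 × 0.073 × f) | Power |
|---|---|---|---|---|
| 0 | 12.5% | 8.1% | 0 | 0.80 |
| 10% | 11.8% | 7.7% | 5.5 | 0.77 |
| 20% | 11.0% | 7.2% | 11.0 | 0.74 |
| 30% | 10.3% | 6.7% | 16.6 | 0.71 |

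This overstates the loss somewhat. Like the protocol's own sum, it treats TB and death as separate events, yet a participant whose TB is not counted and who later dies still has a primary event.

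**The case against.** **The lists are not confined to study tests.** A reader might infer that they fit study testing only and that TB confirmed in care is therefore scored as no TB. The text does not support this. Outcomes sets no condition on who ordered the test, and diagnoses made in care are extracted from the record. Culture, non-trace Ultra, two traces or LAM obtained in a clinic all count towards the primary endpoint.

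**The cartridge premise is general.** The sentence on standard cartridge or Ultra describes programmes in high-burden countries and explains why baseline sputum is not cultured. It does not say what the three Kampala clinics use. This stands: if they use Ultra only, no event is lost through the cartridge.

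**A single trace is not an oversight.** A reader might also want a single trace found in care to count as confirmed TB, since a repeat is arranged only for study specimens (at baseline, "we will perform repeat Xpert Ultra testing on the second spot sputum specimen"). But no definition accepts one trace, even where the study refers the participant for treatment, and a clinic can produce two traces. The rule is deliberate.

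**Bias between arms is not shown.** Differences in cartridge between clinics would be a site effect. Randomization is stratified by site, the analysis is adjusted for site, and routine clinic staff are blinded. This stands for the primary endpoint.

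**Month 24 tests sputum only.** Leaving LAM out of that visit's list may simply reflect the specimens collected. That is fair, but it does not explain part A, which covers the whole period after month 3.

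**Detail may sit in unseen documents.** The extraction form, full protocol and analysis plan may classify each routine result. That excuses silence on procedure. It does not excuse lists that are stated in this article and disagree.

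**Conclusion.** The concern holds as a problem of inconsistent and incomplete definitions. LAM counts for the primary endpoint but not for incident TB in Table 2 part A. Culture counts after month 3 but not for prevalent TB in part D, which feeds the primary risk and safety endpoint. Standard-cartridge Xpert counts nowhere, and a participant treated on such a result is not sampled at month 24.

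The LAM and culture discrepancies can be read directly from the text. The size of the cartridge effect cannot: it depends on the clinics' test mix and may be zero. Under the assumption of a 10% to 30% loss of TB events, equal in both arms, power falls from 80% to about 77% to 71%. The protocol's power calculation is itself correct. Aligning the definitions is worthwhile because it is cheap and protects both event capture and the safety count.

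**What to change.** Use one list of confirmatory results in Outcomes, Table 2 parts A and D, and Final TB status assessment, for both time windows: positive culture, positive standard-cartridge Xpert MTB/RIF, one non-trace Xpert Ultra, two trace Xpert Ultra results, or positive urine LAM. Bring the classifying sentence in Prevalent TB status assessment into line. Only the date of diagnosis should then separate prevalent from incident TB.

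Record the test type and result category when diagnoses are extracted from the medical record, if the form does not already do so.

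Keep the two-trace rule for the primary analysis. Optionally, add a sensitivity analysis that counts a single unrepeated trace from routine care, followed by TB treatment, as an event.

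The cost is definition wording, one extraction field, and a look back at test type for participants already followed. The downside is slightly more heterogeneous confirmation of TB.
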